### Process effectiveness

2.13

Achieved HR (Objective Aiv)

Establishing the ability of participants to achieve the appropriate HR will be a key aspect within the evaluation of home‐based HIIT feasibility. Exercise participants will be supplied with a Polar H9 HR monitor, to be used during every home‐based HIIT session. HR will be recorded using the Polar Beat Smart Phone application (downloaded on participant Smartphones), paired to a Bluetooth‐equipped Polar H9 HR monitor, with each session uploaded to Polar Flow online software, and exported as a Microsoft Excel spreadsheet (version 2204). Achieved HR will also be recorded in participant diaries at the end of each HIIT set (three bouts of 45 s).

Rate of perceived exertion (Objective Aiv)

As other factors can affect exercise intensity in PwP, such as motor symptoms and/or deconditioned muscle affecting movement economy,^22^ the self‐reported rate of perceived exertion (RPE) will also be recorded with the 6–20 point Borg Scale^23^ as a secondary measure of achieved intensity. Participants will record RPE in diaries at the end of each HIIT set.

### Safety

2.14

Adverse effects and events (Objective Ai; also refer to Section 2.23)

Adverse effects and events will be the primary measure of safety, which will contribute to the assessment of the practicality of HIIT in the remotely supervised home setting. Adverse effects and events will be patient recorded in participant diaries throughout the 12‐week program, and reported to the CI during fortnightly online drop‐ins.

### Proposed primary outcomes for a full trial

2.15

Mechanistic biomarker: Change from baseline blood serum BDNF (Objectives Bi–Biii, Civ)

Recent evidence suggests that high‐intensity exercise, including HIIT can increase circulating levels of BDNF,^24^ a member of the neurotrophin family of growth factors evinced to have several neuroprotective qualities.^5^ Preintervention blood collection will be undertaken before VO_2max_ testing and other clinical tests, as acute high‐intensity exercise can result in a transient increase in serum levels of BDNF that can take up to 2 h to return to baseline.^25^ Similarly, postintervention measurement will be undertaken at least 24 h after the final HIIT session. Blood serum will be analyzed in favor of blood plasma, as plasma BDNF has been suggested as a more reliable measure for clinical studies due to fewer potential technical influences during blood sample processing.^26^

Blood collection, transportation, and analysis: Two blood samples (6 mL) will be taken by a fully trained phlebotomist during each assessment visit. Samples will be allowed to clot at room temperature for 30 min,^27^ then rapidly centrifuged at 4000 revolutions per minute for 10 min at 4°C. Serum will be pipetted into microtubes (1.5 mL), labeled with the participant study code, date, time, and pre‐ or postintervention. Tubes containing serum will be immediately stored at −80°C, pending analysis.

Sample transportation and BDNF analysis: Analysis will start upon the completion of the HH4P program and collection of all data. Samples will be analyzed at Manchester Metropolitan University (MMU), by the CI, one member of the ST ([name]) and one researcher from MMU. A transfer agreement will be written and signed by the UoP and MMU before shipping microtubes with a professional courier and following the guidance for dry ice shipments. Samples will be analyzed with the BDNF sandwich enzyme‐linked immunosorbent assay kit (Promega).
Progression of motor symptoms: Change from baseline Movement Disorder Society Unified Parkinson's Disease Rating Scale part III (Objectives Bi–Biii, Civ).

The Movement Disorder Society Unified Parkinson's Disease Rating Scale (MDS‐UPDRS) is a clinician and patient‐completed rating tool designed to assess disease severity and progression. The MDS‐UPDRS part III focuses specifically on motor aspects such as rigidity and gait, is evidenced to be internally valid,^28^ and will be utilized in accordance with the official UPDRS III protocol.
Cardiorespiratory fitness: Change from baseline maximal oxygen uptake (VO_2max_) (Objectives Bi–Biii, Civ)

Increased cardiorespiratory fitness is associated with a myriad of putative health benefits in both healthy and clinical populations. However, cardiorespiratory fitness is commonly reduced in PwP,^3^ potentially leading to further health and well‐being complications.

VO_2max_ will be measured by undertaking an incremental exercise test (IET) using a Lode Corival cardiopulmonary exercise testing cycle ergometer. Oxygen consumption and carbon dioxide production will be measured with a face mask connected to a calibrated Cortex 3B‐R3 (Cortex Biophysik). The IET protocol will be as previously described.^11^ Due to the maximal nature of the IET and the potential to influence other results,^25^ VO_2max_ testing will be undertaken last.

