### Study design overview

2.1

This is a randomized controlled parallel group feasibility study with mechanistic, physiological, and clinical subcomponents. Twenty‐four PwP will be randomized in a 1:1 ratio either to the HH4P 12‐week, home‐based HIIT program plus usual care (intervention) or to usual care alone (control). Assessments will include feasibility and safety factors, and pre and postintervention assessments of potential primary and secondary outcomes undertaken by assessors blinded to group allocation. Both groups will undergo objective physical activity (PA) monitoring 1 week before, and in Week 7 of the intervention. Exercise participants will be invited to attend a posttrial focus group constituting a qualitative addition to assessment of intervention fidelity.

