### Blinding

2.21

Participants are unable to be blinded due to the nature of the exercise intervention. Similarly, the CI is unable to be blinded. However, initial baseline assessments for each participant will be undertaken before randomization, and the member of the ST ([name]) undertaking postintervention outcome assessments will be blinded to the participants' allocated group. All assessments will be undertaken in visits arranged independently of any intervention sessions, and away from the participant's home. Every effort will be made throughout to ensure these assessments are blinded, for example, by reminding participants not to discuss their group allocation with the blinded member of the ST. The final unblinding of the ST member who undertook assessments will be after the creation of a locked data set and analysis has been undertaken.

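### The BDNF assay, a proposed primary outcome, is run by three people including the unblinded chief investigator, with no masking of tubes described, and the reason given for choosing serum argues for plasma

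*Protocol article*

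**What the plan says.** **Blinding.** Section 2.1 of the protocol article describes the assessments before and after the intervention as "undertaken by assessors blinded to group allocation". Section 2.21 is narrower. It says of the chief investigator (CI): "Similarly, the CI is unable to be blinded". It names one supervisory-team member, who does the postintervention assessments, as the blinded person. Section 2.20 has each allocation emailed to the CI, who passes it on to the participant.

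**Assay.** Section 2.15 opens the list of proposed primary outcomes with "Mechanistic biomarker: Change from baseline blood serum BDNF". Serum is stored in tubes "labeled with the participant study code, date, time, and pre‐ or postintervention". On who does the work: "Samples will be analyzed at Manchester Metropolitan University (MMU), by the CI", together with one supervisory-team member and one researcher from that university. Analysis waits until the programme and all data collection are complete. No recoding or masking of tubes is mentioned.

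**Matrix.** The same section gives the reason for using serum: "Blood serum will be analyzed in favor of blood plasma, as plasma BDNF has been suggested as a more reliable measure for clinical studies". It goes on to credit plasma with less exposure to technical effects while samples are handled. The handling steps are those for serum, for example "Samples will be allowed to clot at room temperature for 30 min".

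**The concern.** There are two separate issues.

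The first is masking. BDNF is one of three candidate primary outcomes, alongside MDS-UPDRS part III and VO2max. Under Objective Bi its responsiveness helps choose the outcomes for a definitive trial, and section 2.26.1 plans a 95% confidence interval for the effect relative to usual care. If someone who knows the arms handles the samples and decides on repeats, dilutions or excluded wells, that interval no longer has the protection that section 2.1 claims for it. Section 2.2 also makes the CI responsible for data analysis, so one unblinded person helps to produce this outcome and then analyses it.

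The second is the rationale. A sentence that picks serum because plasma is more reliable contradicts itself. A reader cannot tell from it why serum was chosen, and the team planning the full trial would inherit the confusion.

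**Working it through.** The point is textual. The documents give no BDNF variance, effect size or error rate, so there is no plan figure to reproduce. The check sets the sections side by side.

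**Step 1. Does the blinding statement reach BDNF?** Section 2.1 covers the candidate primary and secondary outcomes before and after the intervention. Section 2.15 puts BDNF in the primary list. Read as written, the statement includes BDNF.

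**Step 2. Is everyone running the assay blinded?** No. Section 2.15 names three people, one of whom is the CI. Section 2.21 says the CI is not blinded, and section 2.20 shows that this means knowing each participant's arm. The blinding status of the other two cannot be determined from the text at hand, where names are removed.

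**Step 3. Could the CI tell the arm from a tube?** The label carries no arm. It carries study code, date, time and time point.
- The CI takes written consent (section 2.9).
- Participant numbers follow the order of consent (section 2.20).
- The CI learns each allocation (section 2.20).

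If the study code is the consent-order number, the CI can go from tube to person to arm. The article does not say that the two are the same, so this link is probable rather than shown. Dates and times of visits would help the identification in either case.

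**Step 4. Is there a step that would break the link?** None is described in sections 2.15, 2.20 or 2.21.

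**Step 5. How many samples?** 24 participants × 2 assessment visits = 48 sampling occasions at most. Section 2.5 expects 20 to 24 participants at final follow-up, which gives 24 + 20 = 44 to 24 + 24 = 48 occasions. All pass through the same assay arrangement.

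**Step 6. Which matrix is specified?** The outcome name, the clotting step, the pipetting and the storage all say serum. Only the clause giving the reason points to plasma. The procedure is consistent and the justification is not.

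**The case against.** **On blinding.** The best defence is that section 2.1 refers to the assessment visits. Section 2.21 then defines the blinding as that of one team member at those visits and openly says that the CI is not blinded. On this reading the assay is later laboratory work outside the promise. That reading is possible, but section 2.1 speaks of outcomes without excluding the laboratory one, so the sections still need reconciling. It is also fair that two other people share the assay, that the division of work is not stated, that an ELISA reading is instrument-based, and that the main analyses are descriptive. These facts limit the likely harm but do not supply masking. The room for judgement over repeats and excluded wells is a general point about assays and is not something the article describes.

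A reader might infer that the time point on the label itself breaks the blinding. It does not, since the promise concerns allocation and not time point. Nor does the text support saying that the CI alone runs the assay, or that the BDNF results will be biased.

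**On the matrix.** A reader might infer that BDNF is being measured in the wrong matrix and that its standard deviation would be no use to the full trial. The document does not support either. Serum is specified throughout, the proposed full-trial outcome is itself serum BDNF, and nothing suggests a later switch. Whether plasma really is the better matrix rests on a cited source that is not at hand.

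**On plates.** Concern about drift between assay plates has no footing here. The article says nothing of plates, and that is laboratory detail which a condensed article may leave out.

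**Conclusion.** The concern holds in two parts of unequal weight.

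The main part is that the stated blinding of outcome assessment does not extend to BDNF as the assay is described. At least one of the three people running it knows every allocation, the tubes carry identifying codes, and no masking is mentioned. This touches up to 48 sampling occasions and one of three candidate primary outcomes. The size of any bias cannot be given from the document. That the CI can match code to arm is an assumption, resting on the consent and numbering arrangements. For a feasibility study with descriptive analyses this is a modest gap, worth closing because it costs so little.

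The lesser part is a self-contradictory reason for choosing serum. The most likely explanation is a slip in wording, though the text alone cannot settle it. It calls for reconciliation and is not evidence of a faulty measurement.

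**What to change.** 1. **Mask the tubes.** Before shipping to the assay laboratory, an existing team member who takes no part in the assay replaces the labels with random codes that hide participant, date, time and time point. That person keeps the key and releases it only when the BDNF results are final. Because all samples are held frozen until data collection ends, this can be done in one session. The cost is a small relabelling task and a code list, with no added participants, visits or assays.

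2. **If that is not possible**, either let only staff who are blinded to allocation run and read the assay, or limit the statement in section 2.1 to the outcomes it truly covers and report BDNF as assayed unblinded. The first needs a change in who does the work. The second costs a sentence but leaves the gap open.

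3. **Reconcile the serum sentence in section 2.15 with the procedure before sampling.** If serum is intended, as every step indicates, give a reason that supports serum. If the stated reason is what the team means, the collection steps would have to be revisited. The first, and likelier, course is an edit to one sentence.

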### Proposed secondary outcomes for a full trial

2.16

Lower extremity strength; change from baseline 30 s sit to stand test (30 s STS) (Objectives Bi‐Biii, Civ)

The 30 s STS, commonly used for assessing lower body strength and balance control in older adults and PwP, measures the number of times a participant can stand from a seated position in 30 s. The 30 s STS represents an important functional outcome, as reduced lower limb strength has been associated with both lower exercise and walking capacity in PwP.^29^, ^30^
Activities of daily living: Change from baseline Oxford Participation and Activities Questionnaire (OxPAQ) Acute (Objectives Bi–Biii, Civ)

The OxPAQ acute is a patient‐centric, 23‐item self‐reported questionnaire consisting of items pertaining to activities of daily life and participation, used for patients with a variety of health conditions including Parkinson's. The OxPAQ acute varies from the original OxPAQ in that items refer to a reduced recall period of 1 week compared to four in the original, considered appropriate for this feasibility study to extract a more accurate response from participants. A license to use the OxPAQ acute was kindly granted by the Oxford University Innovation Clinical Outcomes Service.
Maximum HR (HRmax) (Objective Aiv)

HR_max_ will be measured pre‐intervention only, during VO_2max_ testing with a Bluetooth‐equipped Polar H9 HR monitor (Polar). This will enable the calculation of individualized HIIT minimum target intensity (75% HR_max_).^11^
Physical activity level (Objectives Bi and Biii)

As an important confounding variable, participant PA will be objectively measured for both trial arms with activePAL^TM^ accelerometers (activPAL™; Paltechnologies Ltd) for a 7‐day period before the program following initial baseline assessments, and also during week 7 of the program.

### Process evaluation (Objectives Avii and Cvii)

2.17

The following elements of process evaluation are included in this feasibility study, guided by the MRC Process Evaluation of Complex Interventions Guidelines.^13^

Fidelity testing: Data from participants' diaries (exercises undertaken, session frequency and duration, RPE) and HR data will be used to evaluate the quality of the intervention delivery and the degree of concordance between the HH4P protocol and the actual program delivery.

### Qualitative evaluation: participant focus group (Objectives Av, Avi, and Ciii)

2.18

Fidelity testing will be supplemented with the inclusion of a qualitative aspect,^13^ to explore participant perceptions of the intervention. A semistructured focus group (or groups, depending on numbers) will be undertaken involving all exercise participants after final outcome measures.

Focus groups will explore the acceptance of HH4P exercise program and delivery procedures, practicality of intervention resources, and willingness of participants to be randomized. Any possible adaptations will also be identified.

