### Sample size

2.5

As this is a feasibility study, an a priori power calculation to detect a significant between‐group difference in a primary outcome is not appropriate.^17^ Instead, this study aims to gain estimates of the likely rates of recruitment and retention, and variability of the proposed primary and secondary outcomes to inform sample size calculations for a potential full trial (objective Cvi). For this feasibility study, we aim to recruit 24 participants^18^ (12 interventions and 12 usual care controls). It is anticipated that to recruit these 24 participants we will need to telephone screen approximately 37 people, of which approximately 35% (*n* = 13) will be found to be ineligible after screening, leaving 24 people to grant consent, and ultimately be randomized. From other similar studies,^19^ we believe that retention rates will be at least 85%, leaving a likely sample at the final follow‐up of between 20 and 24 participants.

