### Consent

2.9

There will be three layers of consent to this study:
1.Permission to be screened:

PwP interested in participating will be invited to complete an online form which includes a statement of permission to undertake the telephone screening process.
2.Consent to be recruited to the feasibility study:

Written informed consent will be obtained by the CI at the baseline assessment session before any data collection. Having been previously provided with study information via Jisc online, participants will have had the opportunity to review the information sheet and ask any questions before attending the baseline assessment session. Consent will also be sought to contact patients' GP to inform them of participation in the trial.
3.Consent to participate in posttrial focus groups:

Participants will be informed of the postexercise program focus group within the PIS, and consent will be included within the prebaseline informed consent process.

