#### Baseline data

2.11.1

Baseline data will be collected at the initial assessment visit during which eligibility is confirmed and once informed consent is obtained/bespoke health screening questionnaire is completed. The initial assessment visit will take place 1 week before the start of the HH4P program delivery date. The following baseline data will be collected:
Demographic data: Gender, age, ethnicity, home circumstances (who they live with), and employment status (as indications of socioeconomic status).Anthropometric data: Body mass (kg), height (cm), and body mass index will be collected/calculated with validated protocols, using a calibrated stadiometer and digital scales.Lifestyle data: Smoking status.Diagnostic data: Hoehn and Yahr stage.^20^
Medications and comorbidities: All current prescribed medications and dosage will be listed and coded.Blood pressure: If BP results are abnormal according to clinical guidelines,^21^ the participant will rest for 10 min. BP will then be remeasured. If BP is still abnormal the participant will be asked to seek medical appraisal before reapplying for the study. Also, participants will be constantly visually monitored during assessment tests for changes in BP. Guidance on symptoms related to extreme rises or drops in BP will be included in the home exercise support documentation.

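### The focus-group evidence on willingness to be randomised (Objective Ciii) comes only from the exercise arm, so views on being allocated to usual care are not heard

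*Protocol article*

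**What the plan says.** Table 1 lists patients' willingness to be randomised as Objective Ciii. The protocol article approaches it in two ways.

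- **Qualitative.** The heading of Section 2.18 names Objectives Av, Avi and Ciii, and the text says: "Focus groups will explore the acceptance of HH4P exercise program and delivery procedures, practicality of intervention resources, and willingness of participants to be randomized". The session "will be undertaken involving all exercise participants after final outcome measures". Section 2.1 likewise invites exercise participants. Section 2.27 will report the transcripts as findings on willingness, but labels the objective Cv.
- **Quantitative.** Section 2.26.1 uses screening and recruitment data to estimate eligibility, recruitment, retention and consent, and cites Objective Ciii. The CONSORT diagram counts people from expression of interest through eligibility and baseline data to randomisation.

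Section 2.22 asks both arms not to take up other structured physiotherapy or exercise. Section 2.9 covers the focus group before baseline: "consent will be included within the prebaseline informed consent process".

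The screening forecast is in Section 2.5. The study expects to "telephone screen approximately 37 people", of whom about 35% (13) "will be found to be ineligible after screening", "leaving 24 people to grant consent, and ultimately be randomized".

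**The concern.** In a trial of an exercise program against usual care, reluctance to be randomised is mostly reluctance to draw usual care. People who drew the program cannot report on that from experience. They are also asked after finishing, when their view of randomisation may be coloured by having received what they came for. Controls accepted the same randomisation, received no program, and were still asked not to start structured exercise elsewhere. They are the only randomised participants who can say whether that was acceptable, and the qualitative design leaves them out.

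The full trial would use these findings to plan recruitment and to decide how to present the control condition. If the reported theme on willingness comes from one arm, it is likely to be more favourable than the view across both arms, and nothing in the planned qualitative data would reveal this.

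Section 2.5 touches the same question. It treats every eligible person as going on to consent and be randomised, although willingness is listed as something still to be learned.

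**Working it through.** **Who is heard on willingness to be randomised**

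| Group | Consent rate (2.26.1) | Views on randomisation (2.18, 2.27) |
|---|---|---|
| Eligible, not randomised | Counted | Not heard |
| Randomised to usual care (12 planned) | Counted | Not heard |
| Randomised to exercise (12 planned) | Counted | Heard |

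The planned sample is 24, allocated 1:1 (Section 2.5). The focus groups can therefore reach at most 12 of 24 randomised participants (50%), and 0 of 12 controls. The selection affects the right-hand column only. The rate, randomised/eligible, can be formed from the CONSORT counts, whose denominator includes eligible people who went no further.

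**Can controls be reached within the existing design?**

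- Consent for the focus group is taken before baseline (Section 2.9) and so before allocation. It is sought before anyone knows their arm.
- Section 2.22 says controls will attend nothing beyond the trial assessments. A question at the existing post-intervention visit fits that statement. A control focus group would need the statement adjusted.
- Post-intervention assessments are done by a blinded team member (Section 2.21), so the answers must not pass through that person.

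**The screening figure**

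Inputs from Section 2.5: target 24; ineligible share 35%; number screened 37.

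- Plan's figure: 24 / (1 − 0.35) = 36.92, rounded up to 37.
- Check: 37 × 0.35 = 12.95 (13 ineligible); 37 × 0.65 = 24.05 (24 randomised).

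The figure reproduces exactly, with the share of eligible people who consent and are randomised, *c*, set at 100%. In general, the number to screen is 24 / (0.65 × *c*). The documents give no value of *c* below 100%, so these are illustrations only:

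| Assumed *c* | 24 / (0.65 × *c*) | Number to screen |
|---|---|---|
| 100% | 36.92 | 37 |
| 90% | 41.03 | 42 |
| 80% | 46.15 | 47 |
| 70% | 52.75 | 53 |

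**The objective label**

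Willingness to be randomised is Ciii in Table 1 and in the heading of Section 2.18, but Cv in Section 2.27. In Table 1, Cv is recruitment and retention rates and the suitability of procedures.

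**The case against.** The focus group is not the sole source for Objective Ciii. Section 2.26.1 ties that objective to consent estimates from screening data, which include eligible people who are not randomised. Section 2.18 presents the focus group as a supplement to fidelity testing. Controls are not ignored elsewhere: completion is counted in both arms (Section 2.12), how and why people are lost to follow-up is examined (Section 2.19), and reasons for withdrawal are recorded (Section 2.24). Both arms also keep access to web resources after the study (Section 2.31), which may make usual care easier to accept.

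Most of this stands. A reader might infer that Objective Ciii as a whole is answered with bias. The documents do not support that, because the rate comes from the wider screened pool. What the objection does not supply is any view from controls who stay. Discontent strong enough to make someone leave would show in the withdrawal reasons; reservations among those who complete would not.

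A reader might also infer that screening 37 people is too few. That is not shown. The figure is approximate and reproduces arithmetically, and nothing stops screening at 37: the stated constraints are the target of 24 and a 3-month window. The people telephoned have already expressed interest, been directed to the information sheet and agreed to be screened (Sections 2.6 and 2.9), so high consent among them is plausible, if optimistic. Losses at the baseline visit may already sit within the 35%, since Section 2.7 places the in-person checks in the screening process. Nor is a failed blood pressure check necessarily a permanent loss: "If BP is still abnormal the participant will be asked to seek medical appraisal before reapplying for the study".

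**Conclusion.** The point holds for the qualitative part of Objective Ciii. As written, views on willingness to be randomised will come only from people who accepted randomisation and received the program, with 0 of 12 planned controls heard. This follows directly from Sections 2.1, 2.18 and 2.27 and needs no outside assumption. That the resulting picture will be too favourable is a reasonable expectation, but its size cannot be calculated from the documents. No numerical estimate in the study is affected, and the consent rate stands on its own data.

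The screening figure is not an error. It rests on an unstated assumption that every eligible person consents and is randomised. The illustrative 42 to 53 rests on consent shares of 90% to 70%, which the documents do not give, and should not replace 37.

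**What to change.** 1. In Section 2.18, extend the willingness-to-be-randomised topic to usual-care participants. The lightest route is a short exit question at the post-intervention visit, worded identically for both arms and returned sealed or online to an unblinded team member, so that the assessor does not see it. The alternative is one online focus group for controls, with the attendance statement in Section 2.22 adjusted.
2. In Section 2.27, report these answers by arm, beside randomised/eligible from the screening data. If the exit question is not added, describe the focus-group findings as the views of the exercise arm.
3. Optionally, say in Section 2.5 that 37 assumes all eligible people consent, and show the range above as illustration.
4. Reconcile the objective label for willingness between Table 1, Section 2.18 and Section 2.27.

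The cost is a few questions or one online session, some care to protect blinding, and possibly a minor change to participant materials. The sample size, assessments and quantitative analysis are unchanged.
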